### 3.4 METRO Study IDs

The METRO study will have a five digit numerical ID. The 5 digits represent the following: the first digit from the left represents the clinic ID (e.g., 1 for QECH, 2 for Limbe, etc.); the second digit represents HIV status of the woman (1 for HIV negative and 2 for HIV positive); and the third to the fifth digits represent random ID numbers for clients in each clinic ranging from 001 to 500. The numerical IDs will be preceded by 2 characters reading "MG" (e.g., MG11001). For simplicity, the study forms will show only the five numerical ID numbers, but each form will be clearly marked "METRO Study". IDs will be entered in the appropriate boxes (ID boxes are shown on each study form) as follows: e.g., 11001 - not 11,001. The original NVAZ or Chorio study IDs will be entered also on a separate box on the first page of enrollment study form. ***Please note: DO NOT MIX NVAZ OR CHORIO STUDY IDs WITH THE METRO STUDY IDs. EACH STUDY HAS A UNIQUE ID SERIES. BE CAREFUL!!!***

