### 4. Potential risks:

Physical risk. A physical risk might occur from phlebotomy (bruising). In order to minimize risk, blood will be collected by study staff trained in optimal techniques of blood drawing, infection control and health care worker protection. Only disposable needles and vacutainers will be used. Eligible participants will use an intravaginal gel or a gel without the active treatment agent. Participants will be informed that their chances of receiving the active gel is determined by chance (like flipping a coin); half of the women will receive the active gel and the other half will receive a placebo (the inactive gel). The gel is used intravaginally and is approved for treatment of bacterial vaginosis, the disease we are interested in evaluating in this study. The gel is used for five days only once every day at bedtime. No major risks have been reported when used in nonpregnant women. Minor complaints include yeast infection and vaginal irritation.

Psychological risk. These include risk of anxiety and depression during notification of HIV status. Trained counselors and study personnel will be available to provide appropriate counseling and clinical management. Referral to support and social services will be available.

Social risk. Social stigmatization based on knowledge of HIV status of the woman could occur. To avoid discrimination and to conceal the HIV status of the clients, counseling will be performed in private, and all participants (both HIV infected and uninfected) will attend the same clinic and undergo the same study procedures. Women will be free not to answer any question if they feel the information being requested is sensitive. Failure to respond will not impact provision of routine

medical care.

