### 1.5 Advantages of the proposed enrollment scheme

Recruitment of women from the on-going NVAZ and chorioamnionitis perinatal trial populations has several advantages:

- Participating women will benefit from the trial (we will screen for genital infections and provide treatment if indicated);
- Is cost-effective because the existing infra-structure of clinic personnel, counseling and testing, and the same child/mother follow-up arrangements will be utilized;
- Involvement of women in on-going research for the baby could increase rates of retention in these studies because women will become active participants;
- Enrolling both HIV infected and un-infected women in these clinics will maintain confidentiality of participants and eliminate potential discrimination based on HIV status of participants.

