### 3.5. IMPORTANT: ID code and labelling of treatment assignment

This is a masked (blinded) clinical trial - neither you, the investigators or the patient would know who is receiving the Metronidazole or placebo gel. The tube which contains the gel will have the same ID number as assigned on the forms. These IDs are assigned randomly. Each treatment tube will have the following labels: ID # (e.g., MG11001); The METRO Study, and a visit number (e.g., V1, V2, V3, etc.) to show the visit number at which the tube was issued (remember: each woman will receive 4 tubes during the 12 months METRO study period). See example below showing the label which appears on each tube.

**MG11001  
THE METRO STUDY  
V1**

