### 11.1.2 Dosing

Each tube contains 70 g of metroGel-Vaginal. Study participants will be provided a single new product tube and a set of five new applicators at each visit. Women will use a new applicator each time the product is applied (dose 5 g per 5 ml applicator each night for five consecutive nights). The total amount of gel being used after each visit is therefore only about 25 g. Women will be instructed to bring back the tube so that the unused portion of the gel can be assessed.

Women will be instructed to use the product for 5 consecutive nights. The gel use should not be started during menses. If menses starts while the product is being applied, use should be discontinued and re-started when menses stops. If a woman forgets to insert the gel for any reason, she should apply it the following night until a total of five applications have been completed (i.e., all new applicators have been used). Women should be instructed not to clean or wash

the inside of the vagina until the following morning.

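### The study ID printed on every take-home gel tube carries the woman's HIV status in its second digit, which weakens the protocol's aim to conceal that status

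*Protocol*

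**What the plan says.** Section 3.4 of the manual of operations defines the number. After two fixed letters come five digits: the first is the clinic, the last three are a serial number, and "the second digit represents HIV status of the woman (1 for HIV negative and 2 for HIV positive". Sections 5.7 and 12.3 apply the rule by giving each of the five clinics one ID range for HIV-negative and one for HIV-positive women.

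Section 3.5 puts this number on the product: "The tube which contains the gel will have the same ID number as assigned on the forms". It adds: "Each treatment tube will have the following labels: ID # (e.g., MG11001); The METRO Study, and a visit number". It also states that "each woman will receive 4 tubes during the 12 months METRO study period".

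Section 11.1.2 has the product leave the clinic: "Study participants will be provided a single new product tube and a set of five new applicators at each visit". The woman applies the gel on five nights and returns the tube so that the remainder can be assessed. Sections D.2.m and 11.1.1 use the number on the returned tube as a compliance check.

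On confidentiality, section E.4 (social risk) says: "To avoid discrimination and to conceal the HIV status of the clients, counseling will be performed in private". Section E.5 says that ID numbers serve to keep test results anonymous and that results stay confidential. Section 1.5 gives as an advantage of enrolling both HIV groups in the same clinics that this "will maintain confidentiality of participants and eliminate potential discrimination based on HIV status of participants".

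**The concern.** An ID number is meant to stand in for a person without saying anything about her. Here one digit of it is a test result with a fixed, two-valued meaning. On a form in a locked cabinet that matters little. On a tube kept in a woman's home it sits beside the person it describes, where the rules in section 10.3 on locked files and on separating names from numbers cannot reach.

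What is at stake is participant protection. The protocol recognises stigma as a risk and designs around it with shared clinics, identical procedures and private counselling. The label works against that effort for no benefit, because the tube does not need to show the stratum.

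**Working it through.** No power or error-rate figure is involved. The check sets the rules side by side and bounds the number of tubes.

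**1. Is the digit a reliable marker?** Sections 5.7 and 12.3 list ten ranges (five clinics by two HIV groups). The HIV-negative ranges begin 11, 21, 31, 61 and 71; the HIV-positive ranges begin 12, 22, 32, 62 and 72. The second digit therefore gives HIV status at enrolment without exception. No rule changes the ID after seroconversion, so a 1 may later be out of date.

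**2. Does it leave the clinic in readable form?** Section 3.5 prints the full number, and its specimen label shows it uncovered. Section 11.1.2 sends the tube home. No section covers, scrambles or replaces the digit.

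**3. What would a reader need to decode it?**

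| The reader has | What follows |
|---|---|
| All tubes of one woman | One ID repeated; nothing to compare |
| Two women's tubes, same second digit, no other knowledge | Nothing about either woman's status |
| Two women's tubes, different second digit, no other knowledge | The numbers differ; the meaning is unknown |
| Two women's tubes and one woman's HIV status | The other's status could be inferred if the reader takes the digit to be the marker |
| The code itself and one tube | Status at enrolment |

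The fourth row is plausible. Women learn their status before enrolment (section D.2.c), so each participant knows at least one. Section D.2.l also brings together groups of 4 to 6 participants, and of male partners, to talk about product use.

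**4. How many tubes?** Inputs from section 12.4.1 are 832 HIV-infected women, 416 per arm, and losses under 10%; section 3.5 gives four tubes per woman.

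- Plan's retention figure: 416 × 0.90 = 374.4, which it gives as 375 per arm, or 750 per HIV group.
- Ceiling: 832 × 4 = 3,328 tubes.
- With 750 women at each of the three later dispensing visits: 832 + 3 × 750 = 3,082, before any stop for pregnancy.
- Floor, if every woman received only her enrolment tube: 832 × 1 = 832.

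Product stops at pregnancy (sections 11.2.1 and 13.3), and a missed quarterly visit yields no tube (section 3.2.3). The plan assumes that 80% of women become pregnant again but gives no timing within the year, so an expected count between 832 and 3,328 cannot be derived.

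**5. Does it touch the treatment comparison?** Section 12.3 assigns half of each HIV-specific list to active gel and half to placebo. The digit therefore says nothing about treatment arm.

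**The case against.** The strongest case against is that the label shows only a code, with neither a name nor the word HIV. The measures listed in section E.4 (private counselling, one clinic and the same procedures for both groups) all remain in place. Study forms carry the same number, but they are kept in locked files open only to study staff (section 10.3). All of this stands. The coding weakens concealment; it does not cancel the other protections, and the tube is the main exposure.

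Three stronger readings are tempting and are not supported:

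- A reader might infer that any two labels from one clinic break the code. They do not: as the table shows, the reader also needs the code or one woman's status.
- A reader might take 3,328 as the number of tubes that will circulate. It is a ceiling.
- A reader might infer that visible HIV status biases the assessment of bacterial vaginosis. The protocol promises masking to treatment (sections 3.5 and 12.8), never to HIV status. Project nurses run the rapid HIV tests (section 4.2.1), examine the women and take the vaginal samples, and clinics enrol from HIV-specific lists (section 5.7). A neutral number would not hide status from the staff who judge discharge. At most it would affect laboratory readers of clue cells and the amine test, and the documents give neither a mechanism nor a size for a bias there.

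It can also be said that changing tube numbers mid-trial would break the rule that tube and form numbers match, and the compliance check that depends on it. That is fair, and the remedy has to deal with it.

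**Conclusion.** The point holds as a confidentiality weakness in the labelling rule. Each link is stated in the protocol: a fixed HIV digit, the same number on every tube, the tube taken home, and an aim to conceal HIV status and keep results anonymous. Together these mean that a tube could disclose status to someone with the code or with knowledge of one participant's status. It does not follow that tubes will disclose it, and the documents give no basis for a probability.

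The exposure is up to 832 HIV-infected women and between 832 and 3,328 tubes, assuming full recruitment and a tube for every woman at enrolment. Treatment masking, the within-stratum treatment comparison and power are unaffected. The change is worth making because the possible harm is hard to undo and the remedy is cheap.

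**What to change.** Print a status-neutral unique number on the tubes. For new enrolments, preferably make it the study ID as well: one series per clinic, with the two HIV-stratified randomisation lists drawing interleaved, non-overlapping numbers from it. Restrict the lists linking number to stratum to pharmacy, the study statistician and the enrolling staff who need them to choose the right list.

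For women already enrolled, keep the study ID and put a neutral tube number on the remaining tubes, cross-referenced to the ID in the dispensing log. Section 13.4 already has tubes ordered singly, with follow-up tubes ordered two weeks ahead, which leaves time to relabel. Amend sections 3.5, D.2.m and 11.1.1 so that the returned-tube check uses the tube number; otherwise the compliance check fails.

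Stratification by clinic and HIV status, sample size and analysis do not change. The cost is new number lists and labels, an addendum to the manual, a lookup step for staff, and a small added risk of dispensing error that the log must control.

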### 3.5. IMPORTANT: ID code and labelling of treatment assignment

This is a masked (blinded) clinical trial - neither you, the investigators or the patient would know who is receiving the Metronidazole or placebo gel. The tube which contains the gel will have the same ID number as assigned on the forms. These IDs are assigned randomly. Each treatment tube will have the following labels: ID # (e.g., MG11001); The METRO Study, and a visit number (e.g., V1, V2, V3, etc.) to show the visit number at which the tube was issued (remember: each woman will receive 4 tubes during the 12 months METRO study period). See example below showing the label which appears on each tube.

**MG11001  
THE METRO STUDY  
V1**

#### 4.0. PROCEDURE FOR HIV SCREENING

Women to be enrolled in the METRO study would have been counselled and screened for HIV in the NVAZ or Chorio studies, respectively, at time of delivery or antenatally. The HIV screening described here is the same as the one used in the NVAZ or Chorio studies.

##### 4.1. HIV screening

###### 4.1.1 Purpose

- to give introductory information about the project to the mothers
- to counsel women for HIV testing
- to accurately identify women who agree to be HIV tested
- to allow accurate identification of women who are willing to be enrolled in the study
- to obtain written, informed consent for HIV screening (as mentioned previously, the same NVAZ screening consent form is used).

###### 4.1.2 Forms

Two HIV screening consent forms are used in the NVAZ study at time of delivery, and one HIV screening consent form is used antenatally in the Chorio study (See Appendix 1 for a copy of the NVAZ and Chorio screening consent forms).

###### When/where

When women present for delivery or attend first antenatal visit at QECH or health centers around Blantyre.

###### By whom

Project nurses.

###### Eligibility

- resident in Blantyre or surrounding Districts (a study area)
- signed consent form for HIV testing
- willing to receive HIV counselling and learn results of HIV testing
- not participating in other microbicide studies.

##### 4.2. HIV screening test

###### 4.2.1. By whom

- The clinic nurses will collect either maternal blood or infant cord blood for HIV screening.
- Project nurses will perform rapid HIV testing. The Johns Hopkins Project (JHP) laboratory technicians will carry-out confirmatory HIV testing (see Section 7.0).

#### 4.2.2. Supplies needed

- Lancets
- Vacutainers tubes
- Gauze pads
- Rapid HIV test kit.

#### 4.2.3 Description of the procedure

For women who present antenatally or early at time of delivery, a finger prick maternal blood will be collected for rapid HIV testing. For women who arrive late at time of delivery (when there is no adequate time to conduct HIV counseling and testing before delivery) the project nurses will collect infant cord blood (from the placental side of the cord) in a red top vacutainer. This blood will be stored in a locked cabinet until informed consent is obtained from the woman. If the woman consents to be in the study, the infant's cord blood will be tested for HIV using a rapid test (see Section 7.0). If the woman does not consent, the stored blood sample will be properly and safely discarded.

#### 4.2.4 Post-test counselling

Women will be post-test counselled as soon as the results of rapid HIV test are available. The women will be recounselled when the result of the confirmatory HIV test is available.

## 5.0. PROCEDURES FOR OBTAINING INFORMED CONSENT AND ENROLLMENT IN THE METRO STUDY

As indicated earlier, woman currently being screened for the NVAZ or Chorio studies will be eligible for enrollment in the METRO study. Although no formal consent form will be signed until 3 months after delivery (i.e., at V 3), potential participants will have the opportunity to hearing about the METRO study on several occasions during the general health talks provided antenatally and postnatally for all women attending any of the study clinics. JHP nurses will conduct health talks antenatally and postnatally and provide a brief description about the METRO study in Chichewa (local language). Interested women will be advised that they will be formally counselled to enrol at 3 months after delivery.

### 5.1 Purpose

To explain the project to women and to offer them the opportunity to participate in the METRO study if they understand the protocol and desire to participate.

### How

All women will receive a health talk on issues related to mother and child health including contraception, breastfeeding and HIV transmission. This will be followed by an individual confidential counselling to know about the study details including visit schedules and procedures involved, and to confirm willingness to enroll in the METRO study. See Appendix 2: copy of METRO enrollment consent form.

### 5.3 By whom

Project nurses trained and certified in the principles of counselling and obtaining informed consent.

### 5.4 To whom

To women who fulfil the eligibility criteria to be enrolled in the study.

### 5.5 Informed consent procedure

- Explain the purpose of the study
- Explain the procedures and visits which are involved in the study
- Explain any risks and benefits involved with the study
- Answer the woman's questions and address any concerns
- Any participant who decides to enroll in the study must provide a written informed consent or thumb-printed consent
- A copy of the consent form is provided to all participants.

### Storage of consent forms

- Consent forms are taken to the project office at the end of each day
- Signed consent forms should be filed in chronological order, by ID number in the project office
- Consent forms should be kept in a locked file

The Field Director (or designee) will make periodic checks of the consent forms and initial checked forms.

Any missing consent forms are considered a violation of ethical guidelines and the responsible individuals will be subject to disciplinary action.

## 5.7 Enrollment procedures

Each woman enrolling in the METRO study is systematically assigned to next available ID. For example, if the first HIV negative woman is assigned ID 11001, the next HIV negative woman should be assigned ID 11002. Similarly, if the first HIV positive woman is assigned ID 12001, the next HIV positive woman should be assigned ID 12002.

Each clinic will receive two separate lists of IDs; one list of IDs for randomization of women who are HIV negative, and another list of IDs for randomization of HIV positive women. See listing below for each clinic::

| Clinic | Code | ID Range HIV -ve | ID Range HIV+ve |
|---------------|-------------|-------------------------|------------------------|
| QECH          | 1           | 11001-11500             | 12001-12500            |
| Limbe         | 2           | 21001-21500             | 22001-22500            |
| Cholomoni     | 3           | 31001-31500             | 32001-32500            |
| Zingwangwa    | 6           | 61001-61500             | 62100-62500            |
| Ndirande      | 7           | 71001-71500             | 72001-72500            |

Within these ID ranges assigned to each clinic, women are randomized to receive either the active product or placebo.

## 6.0 PROCEDURES FOR PHYSICAL EXAM

6. A general physical clinical examination and a pelvic examination will be performed.

6.2 Purpose

To document baseline physical condition of the study participant and to detect any abnormal clinical conditions during the progress of the study. A systematic clinical evaluation of the participant will include examination of the head and neck (including oral exam), upper limbs, thorax, abdomen and groin, and lower limbs. The examination will also include external genitalia, a speculum-aided vaginal inspection, and bimanual vaginal exam.

6.3 When

At enrollment and each subsequent visit.

6.4 Where

At the participating clinics.

6.5 By whom

Project nurses trained and certified in study procedures.

6.6 To whom

Women who have consented to be enrolled in the METRO study.

6.7 Supplies needed

- Thermometer
- Sphygmomanometer
- Speculum
- Adult weight scale
- Measuring tape
- Adjustable good light source.

6.8 Description of procedures

- Women will be informed of the procedure to be undertaken at each exam session.
- Weight and height are obtained in a standing position. The weighing scale will be regularly checked and recalibrated as necessary.
- Participant will rest comfortably on a standard examination couch.
- Temperature and blood pressure are measured.
- A routine general physical exam is performed and followed by a pelvic exam.
- The following steps are followed in a pelvic exam (record all findings adequately on appropriate forms):

- ▶ Palpate inguinal lymph nodes for enlargement and tenderness
- ▶ Visually inspect vulva and perineum for ulcers, rashes, vesicles, warts, or other lesions. Examine the genitalia and surrounding skin for evidence of scratching due to itching  
Inspect vaginal introitus for discharge and odor; note redness, itching marks, etc.
- ▶ Insert a speculum lubricated with water into the vagina  
Inspect visually the inside of the vagina and cervix for discharge (describe color, odor, source, quantity), redness of mucosal surface, breaks in the mucosal surface, bleeding (describe color [e.g., is it fresh blood], quantity, site/source of bleeding), ulcers (describe shape, size, location, bleeding, etc.), warts or any other lesions (look for scratches and evidence of trauma)  
Include in your inspection examination of the vaginal fornices and the cervix. For the cervix report on any discharge (describe as above), mucosal surface abnormalities such as redness, friability, ectopy, ulcers or any other lesions  
While inspecting the inside of the vagina observe and report presence of the study product (the gel), or if there is any evidence to suggest use of traditional vaginal products
- ▶ Finally perform a bimanual vaginal exam and report on any tenderness on bimanual exam, size of the uterus, presence of any masses, or other abnormal findings.

